## Abstract

**Background:**

The diabetes of many patients is managed in general practice; healthcare providers aim to promote healthful behaviors, such as healthful diet, adequate physical activity, and smoking cessation. These measures may decrease insulin resistance, improve glycemic control, lipid abnormalities, and hypertension. They may also prevent cardiovascular disease and complications of diabetes. However, professionals do not adhere optimally to guidelines for lifestyle counseling. Motivational interviewing to change the lifestyle of patients with type 2 diabetes is intended to improve diabetes care in accordance with the national guidelines for lifestyle counseling. Primary care nurses will be trained in motivational interviewing embedded in structured care in general practice. The aim of this paper is to describe the design and methods of a study evaluating the effects of the nurses' training on patient outcomes.

**Methods/Design:**

A cluster, randomized, controlled trial involving 70 general practices (35 practices in the intervention arm and 35 in the control arm) starting in March 2007. A total of 700 patients with type 2 diabetes will be recruited. The patients in the intervention arm will receive care from the primary care nurse, who will receive training in an implementation strategy with motivational interviewing as the core component. Other components of this strategy will be adaptation of the diabetes protocol to local circumstances, introduction of a social map for lifestyle support, and educational and supportive tools for sustaining motivational interviewing. The control arm will be encouraged to maintain usual care. The effect measures will be the care process, metabolic parameters (glycosylated hemoglobin, blood pressure and lipids), lifestyle (diet, physical activity, smoking, and alcohol), health-related quality of life, and patients' willingness to change behaviors. The measurements will take place at baseline and after 14 months.

**Discussion:**

Applying motivational interviewing for patients with diabetes in primary care has been studied, but to our knowledge, no other study has yet evaluated the implementation and sustainability of motivating and involving patients in day-to-day diabetes care in general practice. If this intervention proves to be effective and cost-effective, large-scale implementation of this nurse-oriented intervention will be considered and anticipated.

**Trial registration:**

Current Controlled Trials ISRCTN68707773.

## Background

Professionals' performance in lifestyle counseling is suboptimal, yet it is very important that healthcare providers promote healthful behaviors for patients with type 2 diabetes[1,2]. There are studies indicating that healthful diet and physical activity decrease insulin resistance and improve glycemic control, lipid abnormalities, and hypertension, thereby lowering the risk of cardiovascular disease (CVD) [3-6]. Smoking is known to be particularly dangerous; it doubles the risk of CVD for those with and without diabetes[7]. Lifestyle counseling requires more focused support for professionals so that they can adequately support their patients[8,9].

With the increasing prevalence of diabetes due to aging and the increasing average weight in the population, the problems of lifestyle counseling are becoming more urgent[9]. Diabetes mellitus is a major cause of morbidity and mortality worldwide. About half a million people are known to have diabetes in the Netherlands, and this number is expected to increase by 36% in the next 20 years[10]. The age- and sex-adjusted prevalence of type 2 diabetes is 2.9%; 3.1% for women and 2.7% for men[11]. Patients aged more than 70 years account for almost 50% of all patients with type 2 diabetes [11].

Effective diabetes care is based on two elements: structured care and a patient-centered approach [12-14]. These elements lead to improvements of patient outcomes and process outcomes, and they play an important role in lifestyle counseling for diabetes patients [15-17]. In the Netherlands, diabetes care is provided mainly in primary care (80–90%), and in most practices, a primary care nurse has the tasks of providing lifestyle counseling in a structured manner and involving patients in managing their disease[18,19]. Nevertheless, some studies suggest that many healthcare providers, nurses included, lack the skills to promote lifestyle change [20-24]. A practical tool such as the patient-oriented counseling technique of motivational interviewing (MI) can contribute to implementing the lifestyle recommendations[20,25]. Controlled trials in general practices have shown that MI is an effective strategy in the treatment of various diseases [26-30]. However, just training primary care nurses in MI will not be sufficient; it is important to embed MI in an implementation strategy[13].

There is a wide range of implementation strategies aimed at improving the provision of diabetes care in primary care. Multifaceted professional interventions (such as counseling, auditing, and feedback) and organizational interventions (such as revision of professional roles, changes in medical record systems, and arrangements for follow-up) that facilitate the structured and regular review of patients have proven to be effective in improving care[13]. However, very few studies have focused on integrating some of these implementation strategies effectively into professional behavior in daily work in general practice.

Our Motivational Interviewing to Change the Lifestyle of Patients with Type 2 Diabetes (MILD) Study is intended to improve type 2 diabetes care in accordance with the national guidelines for lifestyle counseling by having primary care nurses, who will be trained in lifestyle MI and who will implement structured care in general practice. The impact of the implementation strategy will be evaluated in various ways. First, the effect of the implementation strategy on the nurses' care and the relevant patient outcomes will be examined and compared with those of usual care. Second, there will be a process evaluation of the exposure of the implementation strategy and its feasibility. Third, since this study will determine both the effects and the costs of the implementation strategy, we plan to evaluate it economically to establish the cost-effectiveness. The aim of this study protocol is to describe the design and methods of a study to evaluate the effects, costs, process, and cost-effectiveness of an implementation strategy for motivating and involving patients in lifestyle issues as a part of their diabetes management.

Our research questions will be:

1. What is the effect of an implementation strategy aimed at the routine MI by primary care nurses compared to usual care with regard to:

(a) The care process

(b) The metabolic parameters, such as glycosylated hemoglobin (HbA1_c_), blood pressure, and lipids

(c) Lifestyle changes; diet, exercise, smoking, and alcohol consumption

(d) Health-related quality of life

(e) Patients' willingness to change behaviors? [Effect evaluation]

2. To what extent do primary care nurses take part in the implementation strategy, and is the strategy feasible in the view of patients and nurses? [Process evaluation]

3. What is the incremental cost-effectiveness ratio of our implementation strategy compared with that of the usual care of a primary care nurse? [Economic evaluation]

## Methods/Design

### Study design

The study is a cluster, randomized, controlled trial involving 70 general practices and 700 patients with type 2 diabetes in the Netherlands. Each practice is staffed with a primary care nurse who will be allocated to either:

- The control arm of practices in which patients with diabetes receive only usual care from the primary care nurse.

- The intervention arm of practices in which patients with diabetes receive care from nurses who will be skilled in MI and authorized to use it.

We will include all appointments for each patient (the guidelines require four appointments), so that each patient will be followed for 14 months.

### Ethical approval and informed consent

The Medical Ethics Committee of the University of Nijmegen has granted ethical approval. The trial is registered as ISRCTN68707773[31]. The general practitioner (GP) and the research team will send a letter of information about the project to each eligible patient. The privacy of the participating patients will be protected, and all data will be coded and processed anonymously. It will be made clear in the informed consent form that each patient can stop his of her participation in the study at any moment without any consequence for the quality of his or her usual diabetes care. The patient will be asked to sign the informed consent form and return it to Nijmegen University to allow further contact regarding the research.

### Recruitment of general practices and patients

The trial will be carried out with general practices and their patients with diabetes. Figure 1 shows the pathway with which general practices and patients will be recruited.

**Figure 1 F1:**
[figure not shown]
**Flowchart of the process for recruiting general practices and patients with diabetes**.

#### General practices

Practices in the south of the Netherlands will receive a letter of invitation with an information leaflet about the study. General practices that do not employ a primary care nurse will be excluded from the study. A member of the research team (RJ) will visit all practices that express their intention to participate. At least one GP and the primary care nurse of a practice willing to participate will be present during the appointment. We will explain the study in detail and provide them with a full information package describing the aims, methods, and expected outcomes of the study. Nonresponders will be reminded by letter 4 weeks later. Invitation letters will be sent in several rounds until we find 70 general practices that will participate.

#### Patients

Patients with type 2 diabetes type will be eligible to participate if they are younger than 80 years, their most recent (frequently no longer than a year ago) HbA1_c _concentration is more than 7.0%, their body mass index is more than 25 kg/m^2^, and they are receiving care from a general practice that employs a primary care nurse. Patients with complex coexisting medical conditions (e.g. mental illness or end-stage cancer) and those being treated by an internist will be excluded. Two members of the research team will make a list of all eligible patients in the participating practices by extracting means data from medical files. Each of these patients will be sent a letter with the GP's invitation to participate in the study. The letter will include information about the design of the study, confidentiality of data, the voluntary character of participation, a questionnaire, and the informed consent form. The patients will be asked to respond by returning the signed informed consent form and the completed questionnaire to the research team. Four weeks later, a reminder will be sent to patients who have not responded. Nonresponders will be asked to give their reasons for not participating, so that we can compare the participating and nonparticipating groups.

### Randomization

General practices will be the unit of randomization. An independent person at Radboud University will centrally randomize the 70 general practices in a randomized block design, after the type of practice and urbanization level have been stratified.

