### Sample size

In a regular practice, the proportion of patients with diabetes who have an HbA1_c _concentration greater than 7.0% is about 48%[32]. Lifestyle intervention studies have consistently shown that modest changes in the HbA1_c _concentration can reduce the progression from impaired glucose tolerance to diabetes by about 50%[33]. Therefore, we will aim our program to reduce the proportion from 48% to 24% (50% relative risk reduction). With five patients in each practice, 30 practices in each arm of the study will be needed, if we assume an intercluster correlation of no more than 0.05[34], and set alpha at 0.05 and beta at 0.20.

We also calculated our power on another main outcome; the extent to which patients participate, or are willing to participate, in a program of diet, exercise, and smoking cessation. We predict that the willingness to participate in such a program can at least be tripled on the basis of comparable results of intensive stop-smoking programs in general practice[35]. Just as in smoking cessation studies, we assume that the success of lifestyle counseling in usual care is 5% (relative risk reduction). A power calculation based on the these assumptions shows that we need a total of 68 practices (34 in each arm), with 5 patients in each practice for an implementation strategy based on MI. To answer the research questions, we will take a random sample from the target group; and to take dropout into account, we will include 35 practices in each arm with 10 patients in each practice. Recruitment of 70 practices (700 patients) will be feasible.

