#### Data analysis

Dichotomization of the patient outcomes. The HbA1_c _concentration must be less than 7%; blood pressure, less than 140 mm Hg; the LDL, less than 2.5 mmol/L; and the total cholesterol, less than 4.5 mmol/L [18]. Patients must eat two pieces of fruit and 200 g of vegetables per day, must exercise 30 minutes a day at least 5 days a week, must consume less than 10 energy percent in saturated fat, must not smoke, and must consume no alcohol or only a moderate amount[45]. Descriptive statistics will be used to summarize factors of general practice, primary care nurse and patient factors for the two study arms and to check for comparability in baseline variables between the control arm and the intervention arm. We will use logistic regression techniques accounting for two levels (patient and practice) to statistically compare the intervention and control arms. The baseline measurement will be used in the model as a co-variant. Since different staff members in one practice are involved in the treatment of the diabetes nowadays (care given at practice level), we will have to choose the level of the practice. Exploratory analyses are also planned to examine the effect of explanatory factors (e.g., sociodemographic factors) on the outcome.

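### Practices are randomized within strata of practice type and urbanization, but the stated arm comparison names only the baseline value as covariate; if the strata predict outcome, the test is conservative

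*Protocol article*

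**What the plan says.** Under Randomization, the article states "General practices will be the unit of randomization", and that an independent person will "randomize the 70 general practices in a randomized block design, after the type of practice and urbanization level have been stratified". The number of levels of each factor and the block size are not given.

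Under Effect evaluation, Data analysis, it states: "We will use logistic regression techniques accounting for two levels (patient and practice) to statistically compare the intervention and control arms". The covariate sentence follows: "The baseline measurement will be used in the model as a co-variant". Further factors appear only in the closing sentence: "Exploratory analyses are also planned to examine the effect of explanatory factors (e.g., sociodemographic factors) on the outcome". Neither type of practice nor urbanization level is named as a model term anywhere in the article.

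**The concern.** Stratified, blocked randomization takes differences between strata out of the arm contrast, because each stratum contributes nearly equal numbers of practices to both arms. A model without the strata still counts those differences as between-practice variance. Its standard error then describes a trial without the stratification. Confidence intervals come out wider than they need to be, the true type I error falls below the nominal level, and the trial gets less power than its design has earned.

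The section fixes the type of regression, the two levels, the reason for choosing practice as the second level, and a covariate, and it assigns other factors to exploratory work. Someone implementing it as written would leave the strata out.

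**Working it through.** **Inputs from the article (Sample size).** Intracluster correlation (ICC) at most 0.05; alpha 0.05 and beta 0.20; willingness outcome 5% in usual care, tripled to 15%; 34 practices per arm with 5 patients each; planned recruitment 35 per arm with 10 each.

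**Reproducing the article's figure.** With the pooled two-sided formula, n per arm = [1.96·√(2·0.10·0.90) + 0.8416·√(0.05·0.95 + 0.15·0.85)]² / 0.10² = (0.8315 + 0.3521)² / 0.01 = 140.1, so 141. The design effect is 1 + 4·0.05 = 1.2, and 141·1.2/5 = 33.8, so 34 practices per arm. This agrees with the article.

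**Input not in the article.** R², the share of between-practice variance that the strata explain. It is an assumption throughout and is varied from 0 to 1.

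**Effect on the standard error.** For m patients per practice, the ratio of the SE with strata terms to the SE without them is √{[m·ICC·(1 − R²) + 1 − ICC] / [m·ICC + 1 − ICC]}. Two examples at R² = 0.5:
- m = 5: √[(0.125 + 0.95)/1.20] = √0.8958 = 0.946
- m = 10: √[(0.25 + 0.95)/1.45] = √0.8276 = 0.910

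| R² | m = 5 | m = 10 |
|---|---|---|
| 0 | 1.000 | 1.000 |
| 0.1 | 0.990 | 0.983 |
| 0.2 | 0.979 | 0.965 |
| 0.5 | 0.946 | 0.910 |
| 1 | 0.890 | 0.809 |

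**Effect on power, 5% versus 15%.** With strata terms and R² of 0, 0.2, 0.5 and 1, power is 80.4%, 82.1%, 84.6% and 88.7% at 34 practices × 5, and 95.8%, 96.9%, 98.2% and 99.5% at 35 × 10. The loss is less than the distance from the R² = 0 figure, because stratification narrows the actual spread of the estimate in either analysis. Power without strata terms is Φ(margin/ratio), where Φ(margin) is the power at R² = 0.
- 34 × 5, R² = 0.5: Φ(0.857/0.946) = Φ(0.906) = 81.7%, a loss of about 2.8 points.
- 34 × 5, R² = 0.2: Φ(0.857/0.979) = Φ(0.876) = 80.9%, a loss of about 1.1 points.
- 35 × 10, R² = 0.5: Φ(1.726/0.910) = Φ(1.897) = 97.1%, a loss of about 1.1 points.

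**Simulation check.** Random-intercept logistic model; 70 practices × 10 patients; 48% base rate; ICC 0.05 on the logit scale; six strata (two types × three urbanization levels) and blocks of 4, both assumed; 1,500 replicates; no baseline covariate; critical value 1.96. The odds ratio of 0.62 used for power is chosen for illustration and is not in the article.

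| R² | Model SE, no strata | Empirical SE, no strata | Null rejection without / with strata | Power at OR 0.62 without / with strata |
|---|---|---|---|---|
| 0 | 0.182 | 0.180 | 5.9% / 6.5% | 74.9% / 76.4% |
| 0.2 | 0.181 | 0.177 | 4.2% / 5.2% | 75.6% / 78.1% |
| 0.5 | 0.181 | 0.174 | 4.7% / 6.4% | 74.9% / 80.7% |
| 1 | 0.183 | 0.162 | 2.8% / 4.9% | 76.3% / 83.9% |

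The direction is confirmed. Without strata terms the model SE exceeds the empirical SE by more as R² rises. The gap is smaller than the formula gives: 0.174/0.181 = 0.96 at R² = 0.5, against 0.910. The formula is therefore on the high side for this setup, in which incomplete blocks leave some imbalance. Each empirical SE also carries a Monte Carlo error of about 1/√(2·1500) = 1.8%.

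The power gains should be read with care. With strata terms and a normal critical value, null rejection was 6.5% at R² = 0 and 6.4% at R² = 0.5 (Monte Carlo error about 0.6 points), so part of the apparent gain is a slightly liberal test. Even at R² = 0, where there is nothing to gain, power rose by 1.5 points. For 5% versus 15% with 5 patients per practice, the simulated gain was 0.6 to 1.8 points across all R².

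**The case against.** The strongest objection is that a journal article need not list every covariate. The text does not say that the baseline value is the only one, and an analysis plan that is not shown may include the strata. A reader might infer that the strata are excluded; the article does not say so. What remains is that the section goes beyond a general statement: it sets out the comparison, names one covariate and places other factors under exploratory analyses. Read literally, it does not follow the randomization.

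A reader might also infer that the standard errors are too large as a matter of fact, and that precision is being given away free. The article does not support either. Nothing in it says that practice type or urbanization predicts outcome, and at R² = 0 nothing is lost. The ICC of 0.05 is an upper bound, and a smaller ICC shrinks the effect. The baseline covariate may already absorb part of what the strata would explain. In the simulation the empirical SE was almost the same with and without strata terms (0.172 versus 0.174 at R² = 0.5), so the change corrects the reported SE far more than it sharpens the estimate. The added terms also use practice-level degrees of freedom. All of this stands and limits the size of the point.

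Nor does having 35 practices per arm make the omission worse: the SE ratio depends on m, ICC and R², not on the number of practices. The form in which the baseline value enters the model is a separate question.

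**Conclusion.** The point holds as a low-severity improvement. The stated comparison does not name the factors used to stratify the randomization. If they are prognostic, the reported standard error is too large and the test conservative. Under the formula, at ICC 0.05, the SE with strata terms would be lower by 0% at R² = 0, by about 1–4% at R² of 0.1–0.2, and by about 5% (m = 5) to 9% (m = 10) at R² = 0.5. The ceiling, with the strata explaining all between-practice variance, is 11% and 19%.

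For the 5% versus 15% calculation the cost in power is about 1 to 3 points at R² of 0.2–0.5 with 34 practices × 5. It is about 1 point or less at the planned 35 × 10, where power is already about 96% before any credit for stratification. These sizes rest on an assumed R², on the ICC at its stated upper bound and on near-complete balance within strata; the simulation suggests that the SE figures are on the high side. The error is towards caution, so the validity of the comparison is not in doubt.

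**What to change.** Add one sentence to Effect evaluation, Data analysis: type of practice and urbanization level, as used in the randomization, enter the two-level model as practice-level fixed effects alongside the baseline value. If they are to be left out, give the reason.

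Both factors are known for all 70 practices at randomization, so no data need be collected. The cost is a few practice-level degrees of freedom. With two practice types and three urbanization levels (assumed, since the levels are not stated) there would be three extra terms, leaving 70 − 2 − 3 = 65 rather than 68. As the adjusted test was slightly liberal with a normal critical value in the simulation, a reference distribution based on the practice-level degrees of freedom is worth considering in the same sentence.

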### Sample size

In a regular practice, the proportion of patients with diabetes who have an HbA1_c _concentration greater than 7.0% is about 48%[32]. Lifestyle intervention studies have consistently shown that modest changes in the HbA1_c _concentration can reduce the progression from impaired glucose tolerance to diabetes by about 50%[33]. Therefore, we will aim our program to reduce the proportion from 48% to 24% (50% relative risk reduction). With five patients in each practice, 30 practices in each arm of the study will be needed, if we assume an intercluster correlation of no more than 0.05[34], and set alpha at 0.05 and beta at 0.20.

We also calculated our power on another main outcome; the extent to which patients participate, or are willing to participate, in a program of diet, exercise, and smoking cessation. We predict that the willingness to participate in such a program can at least be tripled on the basis of comparable results of intensive stop-smoking programs in general practice[35]. Just as in smoking cessation studies, we assume that the success of lifestyle counseling in usual care is 5% (relative risk reduction). A power calculation based on the these assumptions shows that we need a total of 68 practices (34 in each arm), with 5 patients in each practice for an implementation strategy based on MI. To answer the research questions, we will take a random sample from the target group; and to take dropout into account, we will include 35 practices in each arm with 10 patients in each practice. Recruitment of 70 practices (700 patients) will be feasible.

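### The 30 practices per arm stated for HbA1c (48% versus 24%) is twice what the stated inputs give: 15 per arm, 30 in total

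*Protocol article*

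**What the plan says.** The Sample size section of the protocol article contains two calculations.

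- **HbA1c.** The usual-practice proportion above 7.0% is put at about 48%, and the plan is stated as: "we will aim our program to reduce the proportion from 48% to 24% (50% relative risk reduction"). The result is given as: "With five patients in each practice, 30 practices in each arm of the study will be needed, if we assume an intercluster correlation" of at most 0.05, and the authors "set alpha at 0.05 and beta at 0.20".
- **Willingness to take part in a lifestyle programme.** Usual-care success is taken as 5% and is expected at least to triple. The result is that "we need a total of 68 practices (34 in each arm), with 5 patients in each practice".

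After both calculations, the section allows for dropout by planning 35 practices per arm with 10 patients each. No dropout rate is given. The abstract confirms equal arms: "35 practices in the intervention arm and 35 in the control arm".

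**The concern.** Halving a proportion from 48% to 24% is a large effect in the middle of the scale. It should need far fewer patients than a change from 5% to 15%, yet the two requirements are printed as nearly equal, at 30 and 34 practices per arm.

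All the inputs to the first figure except sidedness stand next to it, so a reader can check it, and it does not follow from them. HbA1c is treated as a main outcome here, and the Economic evaluation section makes it the primary effect measure. A reader interpreting a null HbA1c result needs to know what effect the stated number of practices was able to detect. Anyone borrowing the figure for a similar cluster trial would start from a requirement that is double what the inputs support.

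**Working it through.** **Inputs**, all from the Sample size section unless noted:

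- p1 = 0.48, p2 = 0.24, difference d = 0.24, mean p = 0.36.
- Alpha 0.05 and power 0.80. Sidedness is not stated; two-sided is assumed, so the normal quantiles are 1.960 and 0.842.
- m = 5 patients per practice and ICC = 0.05 (the stated ceiling), so the design effect is 1 + (5 − 1) × 0.05 = 1.20.
- Allocation 1:1 (abstract).

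**Formula.** Patients per arm, before clustering:

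n = [1.960 × √(2 × mean p × (1 − mean p)) + 0.842 × √(p1(1 − p1) + p2(1 − p2))]² / d²

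Practices per arm = n × 1.20 / 5.

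**Method check on the willingness calculation (5% versus 15%, same ICC, alpha and beta):**

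- n = [1.960 × √0.18 + 0.842 × √0.175]² / 0.10² = 140.1
- 140.1 × 1.20 = 168.1, and 168.1 / 5 = 33.6, so **34 per arm**. This is the article's own figure. With continuity correction it would be 39, so the authors appear to have used the uncorrected formula.

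**HbA1c calculation (48% versus 24%):**

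- n = [1.960 × √0.4608 + 0.842 × √0.432]² / 0.24² = 61.6
- 61.6 × 1.20 = 73.9, and 73.9 / 5 = 14.8, so **15 per arm, 30 in total**. The article states 30 per arm.

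**Variants for 48% versus 24%, m = 5, ICC 0.05:**

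| Variant | Practices per arm |
|---|---|
| Two-sided, pooled variance | 15 |
| Two-sided, unpooled variance | 15 (16 with one extra cluster) |
| Arcsine | 15 |
| t-based cluster power | 16 (79.6% power at 15, 82.2% at 16) |
| Continuity-corrected | 17 (18 with one extra cluster) |
| One-sided | 12 (14 with continuity correction) |
| Alpha 0.025, two-sided | 18 |
| 90% power, two-sided | 20 (22 with continuity correction) |

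No variant at 80% power and alpha 0.05 goes above 18.

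**What 30 per arm would imply:**

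- Effective size: 30 × 5 / 1.20 = 125 per arm. Power for 48% versus 24% is then 98.0%. With 15 practices (effective size 62.5) it is 80.6%.
- At 80% power, 125 effective patients per arm detect 48% versus about 31%.
- To need 150 patients per arm at 80% power, the design effect would have to be 150 / 61.6 = 2.44. That means an ICC of (2.44 − 1) / 4 = 0.36 (0.29 with continuity correction), against the stated ceiling of 0.05.

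**The case against.** The strongest reply is that nothing in the design depends on this number. The error overstates the requirement, 35 practices per arm exceeds both printed figures, and willingness is the larger requirement whether HbA1c needs 30 or 15. That is correct, and it limits the weight of the point. The printed figure still contradicts the inputs in its own sentence, and the margin between the two outcomes is misreported: HbA1c needs fewer than half the practices that willingness needs (14.8 against 33.6).

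Three narrower objections also have some force.

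- **Cause.** That a total was written as a per-arm number is an inference. It is a strong one, because 30 is exactly the total and the willingness sentence keeps total and per-arm counts apart. The method check does assume that ICC, alpha and beta carry over to the second calculation, which the section does not restate. The mismatch does not depend on the cause.
- **The 98% and 31% figures.** They describe 30 practices of 5 patients, not the planned 35 of 10, and they take 48% as given. The eligibility criteria admit only patients whose latest HbA1c is above 7.0%, so 48% may not suit the enrolled group. The figures are best read as a consistency check on the stated inputs, not as the trial's actual power.
- **Dropout.** It cannot explain the figure, because the section brings it in only after both calculations.

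**Conclusion.** The concern holds. On the stated inputs the HbA1c requirement is 15 practices per arm, or 30 in total. The printed 30 per arm is twice that under the uncorrected formula and about 1.8 times under the continuity-corrected one (30 / 16.7). The result assumes a two-sided test; a one-sided test widens the gap. Because 0.05 is the ceiling for the ICC, a smaller value would also lower the requirement.

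This is a reporting error in the sample-size justification. It is conservative: on these inputs it creates no shortfall in power and gives no reason to change the number of practices.

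**What to change.** Correct the HbA1c sentence to *15 practices in each arm (30 in total)*. If 30 per arm was intended, state instead the power it gives for 48% versus 24% (about 98%), the difference it detects at 80% power (48% versus about 31%), or the input that differs from those printed. Add one clause saying that the willingness outcome, at 34 per arm, sets the trial size, and state that the test is two-sided if it is.

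The cost is a sentence or two of text. Recruitment, the 35 practices per arm and the analysis do not change.
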